#### Process evaluation

To evaluate treatment fidelity, a process evaluation will be performed. The Method of Assessing Treatment Delivery (MATD) [57] will be applied, including audio or videotaping treatment sessions to assess protocol adherence. There will be a focus on protocol adherence of the therapists in the MRP condition and a contamination check will be performed to evaluate whether treatments provided in both arms of the trial were indeed different from each other. For treatment fidelity to be adequate, at least 70 % of essential treatment elements must have occurred in order to satisfy the requirements for protocol adherence. Furthermore, maximally 10 % of prohibited treatment elements may have occurred to satisfy the requirements for contamination. Furthermore, satisfaction with the received treatment and the degree of adolescent/family centeredness of the offered interventions will be measured with the Giving Youth a Voice Questionnaire (GYV-20) [58] and Measure of Processes of Care Parent Version short form (MPOC-P-20) [59, 60]. Finally, a comparison will be made between treatment expectation (measured with the Credibility/Expectancy Questionnaire, CEQ-m) [61].

### Data-analysis

#### Statistical analysis

All analysis will be performed on the basis of the “intention-to-treat principle”. Descriptive statistics for demographic and clinical characteristic for both groups (MRP and CAU) and the total group will be used. An inventory of missing data will be made and if necessary an imputation strategy will be chosen.

#### Effect evaluation

Differences after 8 and 16 weeks of treatment will be calculated (short term outcomes), as well as long term outcomes at 10 and 12 months. A linear mixed models approach for calculating differences between baseline and the final follow-up at 12 months will be used. This method used both fixed and random effects in the same analysis. It handles naturally unbalanced data as e.g. uneven spacing of repeated measures and allows analysing the relationship of predictor covariates with the dependent variable (FDI-score). It also accounts successfully for the observed pattern of dependences in the measurements. Appropriate covariates (for the primary outcome potential important imbalances in baseline variables) will be identified in a univariate regression analysis. Before starting the analysis the baseline score of the dependent variable FDI-score and all identified covariates will be centred by subtracting the group mean.

In a first step a fixed effects model will be run and in a second step random effects will be added. Insignificant covariates will then be stepwise removed from the model. Model fit will be assessed with the help of the Bayesian Information Criterion (BIC) and the -2Log likelihood [62].

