## Methods

### Study design and participants

A two group pragmatic randomized controlled trial is undertaken with adolescents with CMP, with follow-up assessment at 2, 4, 10 and 12 months after start of treatment. Adolescents will be allocated to either intervention (MRP) or control (CAU) with a ratio 1:1. Patients who receive an indication for outpatient rehabilitation treatment will be invited to participate and will be randomized to either usual care (CAU) or the intervention (MRP) after informed consent is obtained. Parents will be asked to participate as well.

Estimates for the calculation of the sample size are based on the primary outcome measure, the Functional Disability Inventory (FDI). An average FDI total score of 23 (average score obtained from adolescents that were treated at the Maastricht University Medical Centre in the year before the start of this study), a standard deviation of 9.2 and an expected mean difference between intervention and control condition of 5 points on the total FDI-score were used. A difference of 5 points equals approximately a 25 % difference in mean FDI scores between intervention and control group.

Given α = 0.05, two sided testing, a power of 80 %, and anticipating 15 % loss to follow-up, a sample size of 62 participants per trial-arm was calculated. For two trial arms, this results in a total sample size of *N* = 124.

Adolescents will be recruited from 4 centres in The Netherlands: Maastricht University Medical Centre/Adelante, Laurentius Hospital Roermond, Revant Rehabilitation centre Breda and Rijndam Rehabilitation Centre in Rotterdam. Both treatments offered are embedded in the daily care process in each treatment centre, with an inclusion period of 1.5 years. Ethical approval for this trial was granted by the Medical Ethics Committee Academic Hospital Maastricht/Maastricht University, the Netherlands, NL47323.068.13/METC13-3-062.

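### Effect evaluation gives baseline FDI two roles that do not fit together (reference of a change and centred covariate), and the wording allows models that lose precision or inflate the type I error

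*Protocol article*

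**What the plan says.** The Effect evaluation section describes the estimate in one sentence: "A linear mixed models approach for calculating differences between baseline and the final follow-up at 12 months will be used". It names the FDI score, not a change in it, as the dependent variable, and presents the model as one for repeated measures.

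The same paragraph then states that "the baseline score of the dependent variable FDI-score and all identified covariates will be centred by subtracting the group mean". Grouping baseline FDI with the covariates implies that it enters as a predictor. The next paragraph removes non-significant covariates stepwise and does not exempt baseline FDI.

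The sample size, under Study design and participants, uses "a standard deviation of 9.2 and an expected mean difference between intervention and control condition of 5 points on the total FDI-score were used". It is a plain comparison of two means and gives no correlation between baseline and follow-up.

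**The concern.** A baseline value can serve as a response at time zero or as a covariate. A model that uses it as both needs care, and this paragraph does not say which is meant.

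Two things are at stake:

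- **Precision.** If baseline is a response row, a covariate that is constant within patient cannot affect a within-patient contrast. The intended baseline adjustment would then do nothing for the 12-month effect.
- **Validity.** If baseline is only a covariate, centring on the group mean is harmless when the group is the whole sample, and harmful when it is the arm. The abstract uses group for the trial arms, and the Statistical analysis section uses groups for MRP and CAU and a separate term for the total. The arm reading is therefore open.

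**Working it through.** **Inputs (Study design and participants).** Difference 5, SD 9.2 (read as the SD of a single FDI score), two-sided α 0.05, power 80%, 15% loss, and "a sample size of 62 participants per trial-arm was calculated". The baseline-to-12-month correlation ρ is not given, so a range is assumed.

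**The plan's own figure.** n = 2 × (1.960 + 0.842)² × 9.2² / 5² = 53.15 per arm. Then 53.15 / 0.85 = 62.5, and 53.15 × 1.15 = 61.1, which rounds up to 62. The stated figure is reproduced to within rounding. With 62 × 0.85 = 52.7 completers per arm, SE = 9.2 × √(2/52.7) = 1.792 and 5/1.792 = 2.79. Power is Φ(2.79 − 1.96) = 79.7%.

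**Case 1: baseline is a response row with a free arm difference at baseline, and also a covariate.** Let the mean for patient i at time t be μ(t) + arm × [a + g(t)] + β × baseline(i). The 12-month minus baseline contrast removes β × baseline(i). What remains is the difference in change scores.

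Mixed models fitted to one simulated data set (53 per arm, ρ = 0.3) gave −6.8712, SE 2.0986, both with and without the covariate. The two fits were also identical at ρ = 0.5 and 0.7.

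The relevant SDs are:

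- change contrast: 9.2 × √(2(1 − ρ))
- baseline-adjusted: 9.2 × √(1 − ρ²)

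The variance ratio is 2/(1 + ρ), which exceeds 1 for every ρ below 1. Power with 52.7 per arm (normal approximation):

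| ρ | SD change | SD adjusted | Power change | Power adjusted |
|---|---|---|---|---|
| 0.3 | 10.89 | 8.78 | 65.5% | 83.3% |
| 0.4 | 10.08 | 8.43 | 72.1% | 86.1% |
| 0.5 | 9.20 | 7.97 | 79.7% | 89.6% |
| 0.6 | 8.23 | 7.36 | 87.7% | 93.7% |
| 0.7 | 7.13 | 6.57 | 95.0% | 97.4% |

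Exact t-test values are lower by less than one point. At ρ = 0.5 the change SD equals 9.2, so this is where the change contrast has the planned power. At ρ = 0.3 the change contrast would need 75 completers per arm, or 89 after allowing for loss.

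**Case 2: baseline is a covariate only, centred on the overall mean.** The shift affects only the intercept, and the full gain is obtained. In the same simulated data, change regressed on arm and baseline gave −5.8232, SE 1.6895. This is identical to adjusting the 12-month score, against SE 2.0067 for unadjusted change. The mixed model with follow-up responses only gave SE 1.7094.

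**Case 3: baseline is a covariate only, centred on each arm's own mean.** The covariate is now uncorrelated with arm by construction, so the estimate is the unadjusted difference. The model nevertheless reports the adjusted residual variance, so the SE is too small.

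- Follow-up scores: true SD 9.2, reported 9.2 × √(1 − ρ²). Type I error = 2Φ(−1.96 × √(1 − ρ²)).
- Change scores: true SD 9.2 × √(2(1 − ρ)), same reported SD. Type I error = 2Φ(−1.96 × √((1 + ρ)/2)).

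| ρ | Follow-up scores: formula (simulated) | Change scores: formula (simulated) |
|---|---|---|
| 0.3 | 6.2% (6.0%) | 11.4% (10.7%) |
| 0.5 | 9.0% (8.8%) | 9.0% (8.9%) |
| 0.7 | 16.2% (15.8%) | 7.1% (6.9%) |

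The simulations used 53 per arm, no treatment effect and 8,000 trials per ρ. Standard baseline adjustment stayed near 5%.

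**The case against.** The article never says that baseline is a row of the response vector, nor that the arms may differ freely there. Centring is something done to a predictor, so the intended model may be follow-up FDI adjusted for baseline, with the phrase about differences from baseline describing only the time span. A response-row model with a common baseline mean also avoids the loss. In a small check (15 simulated trials per ρ), its mean 12-month SEs were 1.71, 1.53 and 1.25 at ρ = 0.3, 0.5 and 0.7. The follow-up-only model gave 1.70, 1.52 and 1.25, and the free-baseline model 2.12, 1.77 and 1.36. Under randomisation the change contrast is unbiased and keeps its type I error, so only efficiency is in question there. A full protocol or analysis plan, not shown here, may settle the model.

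Most of this stands, and it rules out two stronger readings that a reader might infer:

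- **That the double use of baseline by itself makes the adjustment worthless.** This is not so: with computed change as the outcome and an overall-centred baseline, the full gain is obtained.
- **That the stated 80% power is wrong.** The documents do not support this. It would need the free-baseline model and a correlation below 0.5, and the article fixes neither.

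What does not stand is that this is only omitted detail. The change contrast and the group-mean centring are both stated. If the follow-up-only model was meant, the sentence about the contrast misdescribes it. The phrase on centring is also not safe under that model if group means arm.

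**Conclusion.** The point holds as a defect of wording in the primary analysis, with consequences that depend on how it is read. Baseline FDI is both the reference of the effect and an implied covariate, and the paragraph does not say which model reconciles the two.

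- With baseline as a response row and a free arm difference there, the adjustment drops out. The resulting contrast is less precise than baseline adjustment at every correlation below 1. Its power is below plan only when the correlation is under 0.5.
- With baseline as a covariate centred within arm, the type I error exceeds 5%: about 6% to 16% for follow-up scores and 7% to 11% for change scores over correlations 0.3 to 0.7.
- With baseline as a covariate centred on the overall mean, there is no problem.

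These figures assume that 9.2 is the SD of a single score, that the SD is equal at baseline and 12 months, and that the correlation lies in the range shown.

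**What to change.** Rewrite the paragraph so that the primary model has one reading:

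- Responses: FDI at 2, 4, 10 and 12 months, with within-patient correlation modelled.
- Fixed effects: arm, time, arm-by-time and baseline FDI.
- Baseline FDI is centred on the mean of all randomised patients, not on arm means. It stays in the model and is exempt from stepwise removal. Other covariates are centred in the same way.
- Report the baseline-adjusted difference between arms at each time point, including 12 months, in place of a difference between baseline and final follow-up.

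This costs one paragraph of rewording before the data are analysed. It needs no new data and no change to the sample size. The resulting estimate is at least as precise as the change contrast at every correlation.

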**Methods/Design:**

Pragmatic multicentre parallel group randomized controlled trial. Randomization by minimization (ratio 1:1) and treatment allocation will be concealed, computer-generated and performed by an independent organization. After randomization, data collection and researchers remain blinded. Inclusion of 124 adolescents and their parents is intended. This sample size is based on a 25 % difference in group mean on the primary outcome, with α = 5 %, β = 80 % and expected 15 % loss to follow up. Study population are adolescents (12–21 years) with CMP with an indication for outpatient rehabilitation treatment in the Netherlands.

The intervention group receives a Multimodal Rehabilitation Program (MRP), a multidisciplinary outpatient individual rehabilitation program. MRP consists of 2 different treatment approaches: A graded exposure module or a combination module of graded exposure and physical training. Selection of a module depends on the needs of the patient. To both modules a parent module is added. The control group receives care as usual, which is the care currently provided in Dutch rehabilitation centres. Treatment duration varies between 7 and 16 weeks, depending on treatment allocation.

Self-reported measurements are at baseline, and at 2, 4, 10 and 12 months after start of treatment. Intention to treat analysis for between group differences on all outcome variables will be performed. Primary outcome is functional disability (Functional Disability Inventory). Secondary outcome variables are fear of pain, catastrophizing, perceived harmfulness, pain intensity, depressive symptoms, and quality of life. Total direct and indirect costs and health related quality of life will be measured. Process evaluation focuses on protocol adherence, patient centeredness and treatment expectations.

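### Centring baseline FDI and the covariates on the group mean, most naturally read as the arm mean, would cancel the baseline adjustment and understate the standard error if baseline enters as a covariate

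*Protocol article*

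**What the plan says.** The Effect evaluation section plans a linear mixed model for FDI up to 12 months, with short-term differences at 8 and 16 weeks and long-term outcomes at 10 and 12 months. Covariates are to be found by univariate regression and are described in parentheses as "for the primary outcome potential important imbalances in baseline variables". Before the analysis, the "baseline score of the dependent variable FDI-score and all identified covariates will be centred by subtracting the group mean".

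The sentence does not say which group's mean is meant. Two other places bear on it. The Statistical analysis section, directly before, announces descriptive statistics "for both groups (MRP and CAU) and the total group will be used", so there a group is an arm and the pooled sample has its own name. The Abstract bases the sample size on a 25% "difference in group mean on the primary outcome", where group mean is again the mean of an arm.

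Under Randomization and allocation concealment, the minimisation factors are centre, sex and age. Baseline FDI is not among them.

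**The concern.** Centring is harmless when one common constant is subtracted from everybody: it shifts the intercept and leaves the treatment effect alone. Subtracting a different constant in each arm is another matter. It removes the between-arm difference in the covariate, which is the very quantity that covariate adjustment uses to correct the treatment estimate. The covariate still explains outcome variation within arms, so the residual variance falls. The model would then attach the smaller standard error of an adjusted analysis to an unadjusted estimate.

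Two things are at stake. The plan selects covariates because of baseline imbalance, and this step would take that imbalance out of the adjustment. Since baseline FDI is not balanced by the allocation procedure, the model is the only protection against a chance difference in it. Second, the primary test could exceed its stated 5% level, with confidence intervals that are too narrow.

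**Working it through.** **Inputs from the Study design and participants section.** "Given α = 0.05, two sided testing, a power of 80" per cent; "a standard deviation of 9.2"; an expected difference of 5 points; "anticipating 15 % loss to follow-up"; 62 patients per arm.

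**Input not in the document.** The baseline to follow-up correlation r of the FDI. It is an assumption here, varied from 0.3 to 0.7.

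**The plan's own figure.** n per arm = 2 × (9.2 × (1.960 + 0.842) / 5)² = 53.15. Allowing for 15% loss gives 53.15/0.85 = 62.5, or 54 × 1.15 = 62.1. The stated 62 is reproduced to within rounding (rounding up to 54 first and dividing by 0.85 gives 64). About 62 × 0.85 = 52.7, so 53 per arm, are expected with outcome data.

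**Algebra under arm-mean centring, baseline as covariate.** The centred covariate has mean zero in each arm, so its covariance with the treatment indicator is zero. Hence:

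- estimate = raw difference in follow-up means, with true variance 2·SD²/n;
- variance reported by the model = 2·SD²·(1−r²)/n;
- ratio of reported to true standard error = √(1−r²);
- actual two-sided type I error = 2·Φ(−1.96·√(1−r²)).

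Example with r = 0.5 and 53 per arm: the true standard error is 9.2 × √(2/53) = 1.79 points and the reported one is 1.79 × 0.866 = 1.55 points. A chance baseline difference of one standard error (1.79 points, at equal SDs) would leave 0.5 × 1.79 = 0.9 points uncorrected in the estimate.

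**Results.** Type I error in per cent at one time point. Simulations used 53 per arm: 20,000 runs of a linear model with one follow-up, and 6,000 runs of a random-intercept model with four follow-ups, tested at 12 months.

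| Assumed r | 1.96·√(1−r²) | Arm mean, formula | Arm mean, linear model | Arm mean, mixed model | Overall mean, linear model | Overall mean, mixed model | Baseline in outcome vector, change tested |
|---|---|---|---|---|---|---|---|
| 0.3 | 1.87 | 6.2 | 6.0 | 5.7 | 4.9 | 4.4 | 5.0 |
| 0.4 | 1.80 | 7.2 | 7.2 | 7.6 | 5.0 | 5.1 | 4.9 |
| 0.5 | 1.70 | 9.0 | 8.7 | 8.6 | 4.7 | 5.0 | 5.0 |
| 0.6 | 1.57 | 11.7 | 11.5 | 11.9 | 4.9 | 4.8 | 5.1 |
| 0.7 | 1.40 | 16.2 | 16.1 | 16.2 | 5.1 | 5.1 | 4.8 |

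In the linear-model simulation, the arm-centred estimate and the raw difference in means never differed by more than 10⁻¹³, which confirms that the adjustment cancels.

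The last column is the case in which baseline FDI is one of the repeated outcomes and group-by-time change is tested. The main effect of a time-constant covariate drops out of a within-patient change, whichever mean was subtracted. The test level is therefore preserved, but the covariates correct nothing in that contrast.

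**The case against.** The strongest reply is that the sentence need not mean the arm. The Discussion uses plain group for the whole patient sample, the arms are elsewhere called conditions or trial arms, and the disputed phrase is singular with no reference to each arm. Arm-centring would make the adjacent covariate step pointless, which is itself a reason to think the overall mean was intended. This stands as far as it goes: the overall mean is a possible reading, and under it nothing is wrong. But the Discussion never joins group to mean. The two places that bear most closely on the phrase, the preceding section and the Abstract, use it for the arm. An analyst following the sentence as written would more naturally subtract arm means.

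A second reply is that the model is described in terms of differences from baseline to 12 months, which may mean that baseline is part of the outcome vector. The test then keeps about 5%. This also stands. Against it, baseline FDI is listed together with the covariates to be centred, which points to its use as a predictor.

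Third, a statistical analysis plan that is not shown may define the mean. That is possible, but the point is not that detail is missing. The article states a rule, and its most natural reading is invalid in a covariate-adjusted model.

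A reader might infer that the primary test is known to run at 7 to 16%, or at a still higher rate for an effect averaged over the four follow-ups. The document supports neither. The first needs the arm reading, baseline as a covariate and an r of 0.4 to 0.7. The second concerns a contrast that the plan does not name; it names separate time points.

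**Conclusion.** The point holds conditionally. On the best-supported reading of the centring rule, and with baseline FDI as a covariate, the treatment estimate is unadjusted, the imbalances for which covariates were chosen stay in it, and the standard error is too small by √(1−r²). The inflation is modest if r is low (about 6% at 0.3) and serious if r is high (about 16% at 0.7). The document does not say where in that range the trial would fall.

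Three assumptions carry the size: group means arm, baseline enters as a covariate, and r takes the assumed value. If the overall mean was meant, the test is sound and only the wording needs repair. If baseline is in the outcome vector and change is tested, the level is sound but the covariates do no work in that contrast. Since the natural reading gives an invalid primary test and the remedy is a single phrase, the sentence should be corrected rather than left to interpretation.

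**What to change.** In the Effect evaluation section, replace the reference to the group mean by the overall mean of all randomised patients (both arms combined), or drop the centring step. Apply this to baseline FDI and every identified covariate, wherever this model is used. The planned mixed model need not otherwise change. If a separate analysis plan already specifies the overall mean, bring the two texts into line.

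The cost is one phrase. No data collection, sample size or patient contact is affected. In the simulations above, overall-mean centring brought the type I error back to about 5% (4.4 to 5.1%).

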### Outcome measures

PedIMMPACT recommendations were followed when choosing outcome domains and in the selection of measurement instruments for this study [45]. Details of measurement instruments can be found in Table 3. Assessments will be performed at baseline (before start of treatment) and at 2, 4, 10 and 12 months after start of treatment. Primary outcome measure is adolescent’s functional disability (FDI) [46, 47]. Secondary outcome measures are adolescent fear of pain (FOPQ-C) [48], perceived harmfulness (PHODA-Youth) [27], pain catastrophizing (PCS-C) [49, 50], pain intensity (VAS) [51], depressive symptoms (CDI) [52] and pain specific quality of life (QLA-CP) [53], and parent perceived functional disability (FDI-P) [46, 47], fear of pain (FOPQ-P) [48], pain catastrophizing (PCS-P) [50], adult responses to children’s symptoms (ARCS) [54].

**Table 3 Tab3:** Primary and secondary outcome measures^a^

Primary outcome	Measurement instrument	Time points of measurement
Functional disability [46, 47]	Functional Disability Inventory (FDI)	Baseline, 8 weeks, 16 weeks, 10 and 12 months
	Self-report measure for perceived difficulty in performing activities at school, at home and in recreational or social interactions.	
	15 Items rated on a five-point scale (0–4). Total scores range 0–60 with a higher scores indicating greater disability.	
	Valid and reliable measure for assessing pain related disability in adolescents.	
ᅟ	ᅟ	ᅟ
Secondary outcomes	Measurement instrument	Time points of measurement
Fear of pain [48]	Fear of Pain Questionnaire (FOPQ-C)	Baseline, 8 weeks, 16 weeks, 10 and 12 months
	Self-report measure to assess pain-related fear in adolescents with chronic pain. 24 items rated on a five-point scale (0–4). Total scores range 0–96 with a higher score indicating more fear. Consists of subscales 1) Fear of Pain and 2) Avoidance of activities.	
	Psychometric properties of the English version are good.	
Perceived harmfulness [27]	PHODA-Youth	Baseline, 8 weeks, 16 weeks, 10 and 12 months
	Measures perceived harmfulness of physical and social activities and can be used to create a hierarchy of fearful activities.	
	51 photographs are rated on a scale 0–10 (steps 0.1). The higher a photo is ranked, the more harmful the adolescent thinks executing the activity is. Consists of subscales 1) activities of daily living, 2) intensive physical activities and 3) social activities.	
	Psychometric qualities are good.	

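### The primary FDI model is built up from the data with random effects, so the within-patient dependence is not secured; if baseline is modelled as a response, the 12-month test could run at about 7-12% instead of 5%

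*Protocol article*

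**What the plan says.** The FDI is measured five times: "Assessments will be performed at baseline (before start of treatment) and at 2, 4, 10 and 12 months after start of treatment" (Outcome measures). Under Effect evaluation, a linear mixed model is to be used for how scores at the 12-month assessment differ from baseline, and differences are also wanted at 8 weeks, 16 weeks and 10 months. The build is sequential: "In a first step a fixed effects model will be run and in a second step random effects will be added". Non-significant covariates are then dropped, and "Model fit will be assessed with the help of the Bayesian Information Criterion (BIC"), together with the -2 log likelihood. Of the mixed model in general the same section says: "It also accounts successfully for the observed pattern of dependences in the measurements".

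The section can be read two ways on the role of baseline. The stated purpose, a difference between baseline and month 12, suggests that baseline is one of the repeated responses. The instruction to centre the baseline FDI score along with the covariates suggests that it is a covariate. The sample size section plans for a 5% level: "Given α = 0.05, two sided testing".

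**The concern.** The standard error of every arm contrast at a visit depends on the covariance the model assumes for the five scores. A random intercept forces one variance and one correlation on all pairs of visits. A random slope lets both change smoothly with time. Neither describes a step, and a step is plausible here. Treatment lasts 7 to 16 weeks (Abstract), so it falls between baseline and about month 4. Baseline may therefore correlate less with the later scores than those scores do with one another.

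If the fitted covariance overstates the baseline-to-follow-up correlation, the standard error of the change from baseline is too small and the test of the primary outcome rejects too often. Building the model up from the data under a fit criterion does not guard against this when none of the candidates fits.

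**Working it through.** **Inputs from the protocol article** (Study design and participants): two-sided α = 0.05, power 80%, difference 5 points, SD 9.2, 15% loss, 62 per arm; visits at 0, 2, 4, 10 and 12 months. **Assumed, because the article gives none:** the within-patient correlations; also equal SD at all visits unless stated, complete data and no true effect.

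**Plan's own figure.** n per arm = 2 × (1.96 + 0.8416)² × 9.2² / 5² = 53.15. Multiplying by 1.15 gives 61.1, rounded up to 62, so the stated number is reproduced. With 15% loss, 62 × 0.85 = 52.7, so 53 per arm are taken as evaluable.

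**Step 1: baseline as a response, random intercept kept.** Let a be the baseline-to-follow-up correlation and b the correlation between follow-ups. Of the 10 pairs of visits, 4 involve baseline and 6 do not. A random intercept fits the average, r = (4a + 6b)/10. The variance of a change from baseline is proportional to 1 − a in truth and to 1 − r in the model. The SE ratio is therefore √[(1 − r)/(1 − a)], and the large-sample size is 2 × [1 − Φ(1.96 × ratio)].

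| a / b | r | SE ratio | Size |
|---|---|---|---|
| 0.50 / 0.65 | 0.59 | √(0.41/0.50) = 0.906 | 7.6% |
| 0.45 / 0.70 | 0.60 | √(0.40/0.55) = 0.853 | 9.5% |
| 0.40 / 0.75 | 0.61 | √(0.39/0.60) = 0.806 | 11.4% |

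In FDI points for the middle row, the true SE of the arm difference in change is √(4 × 9.2² × 0.55/53) = 1.87. The model reports √(4 × 9.2² × 0.40/53) = 1.60.

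**Step 2: does BIC rescue it?** A random slope adds two parameters (its variance and its covariance with the intercept). With 106 evaluable patients, BIC asks for a gain of 2 × ln(106) = 9.3 in -2 log likelihood. In 600 simulated null trials per pattern, with the slope offered as a candidate:

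| Pattern | Slope chosen | Size at 12 months, BIC choice | Size, unstructured |
|---|---|---|---|
| 0.50 / 0.65 | 3% | 7.8% | 4.7% |
| 0.45 / 0.70 | 13% | 10.5% | 5.0% |
| 0.40 / 0.75 | 32% | 9.5% | 5.0% |
| 0.45 / 0.70, follow-up SD 11 | 49% | 8.2% | 5.7% |

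Simulation error is about ±2 points. Further runs of 1,500 and 400 trials per pattern gave 6.6-10.8% and 7-12.5% for the equal-SD patterns. Forcing the slope into the model does not cure the problem (7-9.5%).

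**Step 3: baseline as a covariate, same pattern.** Given baseline, each follow-up has variance 1 − a² and each pair has covariance b − a² (in units of 9.2²). For 0.45/0.70 these are 0.7975 and 0.4975 for every visit and every pair. That is exactly the random-intercept structure, so the large-sample size is 5.0%. Simulated sizes after BIC selection were 3.0-6.4%, against 3.2-7.0% for unstructured.

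**Step 4: correlation decaying with time** (0.71 at 2 months to 0.39 at 12 months). BIC chose the slope in about 99% of runs or more. With baseline as a covariate the sizes were 3.4, 4.9, 4.6 and 2.9% at 2, 4, 10 and 12 months. With baseline as a response and other decaying patterns, the 12-month change test ran at about 3-4%. The largest departure under constant SD was about 8%, for the 4-month change under steeper assumed decay.

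**Step 5: truly equal correlations.** A random intercept is correct and nothing is lost.

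**The case against.** The case against this point is substantial, and much of it stands.

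- *The inflation depends on how baseline is handled.* The centring sentence points to baseline as a covariate, and then the inflation in step 1 disappears (step 3). This stands. The inflation is one reading of an ambiguous section.
- *BIC protects against the error under decay.* This stands for the 12-month contrast. A reader might infer that the trial's tests have sizes anywhere from about 1% to 11%, liberal at 12 months and conservative at 8 weeks. The article does not support that. The low end belongs to a random-intercept model under decay, which BIC rejects when a slope is offered. The high end belongs to a different correlation pattern with baseline as a response.
- *The text does not say that BIC chooses the covariance.* It says fit is assessed with the help of the two criteria. Choosing by them is the natural reading of a stepwise build, but it is an inference. So is any claim that the criteria conflict at particular cut-offs, since no test level for the -2 log likelihood is stated.
- *Covariance structure is usually left to the statistical analysis plan, which is not shown.* This stands as far as it goes, and the missing name of a structure is not the point. The point is the sequence the article does state, and its assurance that the dependence is handled.
- *Random effects with information criteria are common practice.* True, but with five visits common to all patients there is no need to rely on them.

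**Conclusion.** The point holds in a conditional form. The stated build does not secure the claim that dependence is handled. If baseline is a response and correlates less with follow-up (0.40-0.50) than follow-ups do with each other (0.65-0.75), the 12-month change test has a size of about 7-12% instead of 5%. If baseline is a covariate, or if correlations decay smoothly and a random slope is a candidate, size stays near nominal (about 3-6%), apart from the 4-month exception in step 4. With equal correlations there is no error.

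These figures rest on assumed correlations, 53 evaluable patients per arm and complete data, and they ignore the separate stepwise removal of covariates. No test size follows from the article alone. A prespecified unstructured covariance held its size at 2.5-7.0%, which is 5% within simulation error, under every pattern tried, so the trial need not depend on which pattern is true.

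**What to change.** Replace the random-effects step for the FDI by one model fixed before the data are seen:

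- visit as a factor, arm-by-visit interaction, and baseline FDI as a covariate, with the article stating outright that baseline is not a response;
- unstructured covariance over the fixed follow-up visits;
- REML with Kenward-Roger degrees of freedom, and all visit contrasts taken from this one model;
- a named fallback order for non-convergence, for example heterogeneous Toeplitz with robust standard errors. BIC, if kept, is confined to that fallback and applied without sight of the treatment estimate.

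The cost is wording only. Four follow-up visits need 4 × 5/2 = 10 covariance parameters; five visits with baseline as a response would need 5 × 6/2 = 15. The planned 124 patients can support either. Non-convergence should be rare and is covered by the fallback.
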